# Diabetes Intervention Accentuating Diet and Enhancing Metabolism (DIADEM-I): a randomised controlled trial to examine the impact of an intensive lifestyle intervention consisting of a low-energy diet and physical activity on body weight and metabolism in early type 2 diabetes mellitus: study protocol for a randomized controlled trial

**DOI:** 10.1186/s13063-018-2660-1

**Published:** 2018-05-21

**Keywords:** Type 2 diabetes mellitus, Obesity, Lifestyle, Diet, Physical activity

## Abstract

**Background:**

Type 2 diabetes mellitus (T2DM) and obesity are syndemic and will have a significant impact on affected individuals and healthcare services worldwide. Evidence shows that T2DM remission can be achieved with significant weight loss in those who are younger with early diabetes and requiring fewer medications for glycaemic control. DIADEM-I aims to examine the impact of an intensive lifestyle intervention (ILI) using a low-energy diet (LED) meal replacement approach combined with physical activity in younger individuals with early T2DM.

**Methods:**

The planned study is an ongoing, non-blinded, pragmatic, randomised controlled, parallel-group trial examining the impact of an LED-based ILI on body weight and diabetes remission in younger (18–50 years) T2DM individuals with early diabetes (≤ 3-year duration). The ILI will be compared to usual medical care (UMC). The primary outcome will be weight loss at 12 months. Other key outcomes of interest include diabetes remission, glycaemic control, diabetes complications, cardiovascular health, physical activity, mental health, and quality of life. It is planned for the study to include 138 subjects for assessment of the primary outcome. Safety will be assessed throughout.

**Discussion:**

If DIADEM-I demonstrates a clinically significant effect for younger individuals with early T2DM, it will inform clinical guidelines and services of the future for management of T2DM.

**Trial registration:**

ISRCTN: ISRCTN20754766 (date assigned: 7 June 2017); ClinicalTrials.gov, ID: NCT03225339 Registered on 26 June 2017.

**Electronic supplementary material:**

The online version of this article (10.1186/s13063-018-2660-1) contains supplementary material, which is available to authorized users.

## Background

Obesity and type 2 diabetes mellitus (T2DM) are the greatest challenges to health services worldwide. Obesity is associated with multiple complications including T2DM, hypertension, dyslipidaemia, non-alcoholic fatty liver disease (NAFLD), obstructive sleep apnoea (OSA), cardiovascular disease (CVD), chronic kidney disease (CKD), increased risk for several cancers, poor mental health, and reduced quality of life [1–8]. Overall, obesity is associated with early mortality [2].

Of particular concern is the increasing prevalence of obesity at a younger age. The onset of obesity at a young age results in significant morbidity and mortality [9–12]. In a cohort of young men (*n* = 6502, age 22 years) followed up in Denmark, 48% of those who were obese (Body Mass Index, BMI ≥ 30 kg/m^2^) had developed diabetes, cardiovascular disease, or venous thromboembolism, or had died before the age of 55 years [13]. In a cohort of healthy young men (*n* = 37,674), there was an independent association between elevated BMI at age 17 years and angiography-proven coronary heart disease (β = 1.355, *P* = 0.004) [12].

Diabetes at a younger age is associated with greater risk of devastating macro- and micro-vascular complications [9, 14–16]. In an Australian study [17], the outcomes for 354 T2DM patients with early onset diabetes (aged 15–30 years) were compared to type 1 diabetes (T1DM) patients with a median follow-up of greater than 20 years. Those with T2DM had almost double the mortality compared to the T1DM group (11% vs. 6%). Furthermore, death in the T2DM group occurred after about 10 years’ shorter disease duration than the T1DM group. There were more cardiovascular deaths (50% vs. 30%), and increased neuropathy, in the T2DM group. A study of UK primary care data reported that the adverse cardiovascular risk profiles of the younger-aged (mean age 33.8 years) group were similar to the older group (mean age 66.9 years) [18]. A Swedish population-based study reported that those with T2DM had three times greater risk for severe retinopathy compared to those with T1DM [19].

The current medical approach to T2DM concentrates on symptom control, targeting glycosylated haemoglobin (HbA1c) levels, and prevention of long-term diabetes complications [20]. The combination of intensive glycaemic control and earlier introduction and intensification of insulin treatment has resulted in the development and exacerbation of obesity amongst patients with diabetes [21]. This has created a vicious cycle of obesity and T2DM since greater obesity results in greater requirement for treatments that promote weight gain [22].

Weight loss and lifestyle change are important for managing glycaemia, dyslipidaemia and hypertension after diabetes has developed [23–27]. Weight loss through lifestyle interventions and bariatric surgery has been shown to have a significant impact on T2DM [23, 28–32]. More intensive lifestyle and structured interventions show the greatest benefit for weight loss and glycaemic control [24, 25, 33, 34].

The Look AHEAD study [23–26, 35] examined the impact of an intensive lifestyle intervention (ILI) on cardiovascular outcomes. The study aimed for a weight loss of at least 10% through energy restriction and physical activity [35]. In this study, improvement in glycaemia was associated with degree of weight loss. Furthermore, diabetes remission occurred in 11.5% and 7.3% of the ILI group at year 1 and years 4, respectively, compared to the 2.0% of the control group for both time-points [36]. The ILI group also had a significantly greater percentage of sustained remission, although only 3.5% achieved this at 4 years [36]. The subjects in the Look AHEAD study, however, were older (mean age 58.6 ± 6.8y in the ILI group) and had a median diabetes duration of 5 years (2.0–10 years). A less intensive lifestyle intervention in the UK primary care setting observed modest improvements in glycaemia, but did not observe any diabetes remission [33, 37]. Again, this study was conducted in an older group with mean age of 60.1 (SD 10.2) years for the intervention group. Data from bariatric surgery support the hypothesis that any intervention aiming to have an impact on diabetes remission needs to concentrate on younger patients at an early stage of disease [28, 29, 38–41]. It can be hypothesised that intervention at a younger age and earlier disease stage may result in greater improvement and remission of diabetes.

There is significant evidence that substantial initial weight loss is associated with greater long-term net weight loss [24, 42–45]. A retrospective study of 5965 individuals who undertook a very-low-energy diet (VLED; < 800 kcal/day), the weight lost in the initial weight loss phase was significantly associated with the percentage weight loss maintenance for up to 3 years [46]. In the Look AHEAD study, larger monthly weight loss during the first year, independently predicted weight, HbA1c, HDL-cholesterol, and systolic blood pressure at year 4. Thus, greater initial weight loss is a key factor in weight loss maintenance and distal metabolic outcomes. In the Look AHEAD study, successful lifestyle subjects used meal replacement products and attended more frequently. Also, those who lost most weight and maintained their weight, undertook more physical activity [24, 25, 47].

VLED and low-energy diets (LED) are most effective at achieving substantial initial weight loss. A recent study showed that there was no difference in subsequent weight regain between rapid and gradual weight loss [48]. A meta-analysis of 29 studies from the United States observed that weight loss with VLED resulted in greater weight loss maintenance compared to hypo-energetic balanced diets: 7.1 kg (95%CI: 6.1–8.1 kg) and 2.0 kg (1.5–2.5 kg), respectively [42]. In six studies, those who exercised more, had greater weight loss maintenance [42]. VLEDs have been employed in the last 40 years for rapid weight loss and their use in the management of obesity has been recognised by several guidelines [49]. In a systematic review and meta-analysis, six randomised controlled trials were identified [50], and when VLEDs were compared to LEDs, VLEDs resulted in greater weight loss than LEDs in the short term, but similar long-term weight loss. A recent study has reported that an LED approach is as effective as VLED [51]. LEDs are likely to be better tolerated than VLED by patients because of side effects [52, 53], thus improving diet adherence and reducing patient dropout. Common adverse events related to low-energy diets include dizziness, sensitivity to cold, fatigue, dry skin, halitosis, constipation, diarrhoea, flatulence, gallstones, and hair loss [52, 53].

An early study of insulin-treated type 2 diabetes patients, reported that a VLED approach resulted in significant weight loss and cessation of insulin in some patients [54]. A recent large feasibility study in the UK in patients with extreme obesity also observed that a programme based on a nutritionally complete LED (Cambridge Weight Plan, UK) achieved a significant early weight loss and a substantial weight loss of ≥ 15 kg maintained at 12 months for one third of all patients entering the programme [55]. The subjects in this study were 45.7 ± 10.7 years old with more severe obesity (mean BMI 48.0 ± 7.6 kg/m^2^). No specific physical activity was included. Another recent study showed that 8 weeks of calorie restriction (600 kcal/day) in severely obese patients with type 2 diabetes, normalised pancreatic beta-cell function and improved insulin suppression of liver glucose production [56]. A key finding was the association of beta-cell function improvement with alterations in liver and pancreatic fat. The role of the liver in diabetes is, therefore, important [57, 58].

Physical activity is important for weight loss and its maintenance, and has beneficial cardiovascular effects [59]. The addition of physical activity to energy restriction for weight loss in overweight/obesity was examined in a systematic review [60]. The combination of diet with physical activity resulted in greater weight loss than diet alone with the intervention and after 1 year of follow-up.

A systematic review examined the impact of the combination of diet, aerobic activity, and resistance training for type 2 diabetes prevention. The combination was found to be superior for weight loss and reduction in fasting glucose [61]. A recent systematic review (47 randomised trials with over 8500 subjects) examined different exercise interventions on glycaemic control [62]. Exercise interventions of greater than 150 min/week were found to be most effective. Exercise training consisting of aerobic exercise, resistance training, or both combined was associated with reductions in HbA1c compared to control groups, respectively. Unsupervised exercise combined with dietary intervention was associated with an HbA1c reduction. Another systematic review [63] examined studies that have compared aerobic to resistance exercise in T2DM. Twelve trials (*n* = 626 subjects) were identified with seven having methodological limitations. The majority of the studies were short term (< 6 months). With sensitivity analysis, there was no significant difference in HbA1c reduction between the two exercise approaches.

A recent systematic review examined the impact of combined aerobic and resistance exercise in T2DM, including 14 trials (*n* = 915 subjects). Aerobic exercise was more effective than resistance training in HbA1c reduction. Combined treatment, however, was superior to aerobic exercise [64]. The same group carried out a systematic review of long-term lifestyle interventions, reporting that the combination of diet and physical activity was superior to all other modalities resulting in an improved lipid profile and reduction in blood pressure, conferring additional cardiovascular benefit [65].

In summary, the combination of physical activity with diet results in greater weight loss and metabolic improvements. Aerobic exercise has greater and more predictable effects on HbA1c. The combination of aerobic exercise with resistance training may be superior the aerobic exercise alone, but more evidence is required. Based on current evidence, the American College of Sports Medicine and American Diabetes Association (ADA) joint position stand [66, 67] and other guidelines [68] recommend a combination of aerobic and resistance exercise.

### DIADEM-I Study rationale

Emerging evidence suggests that it is time to rethink the medical approach to patients with T2DM. Patients with obesity and T2DM who have achieved significant weight loss through either an ILI or bariatric surgery can have remission of diabetes, and improved quality of life. ILI in the Look AHEAD study resulted in a modest diabetes remission, but the study population had an average age of about 60 years, and longer duration of diabetes. There is extensive evidence that the use of LEDs, and particularly those with low carbohydrate content, can safely result in significant weight loss. There is also evidence to support a role for physical activity in improving diabetes. It is now time to put this evidence into practice through a randomised controlled trial to investigate whether combining energy restriction with physical activity in younger patients at an early stage of T2DM can improve weight loss and diabetes outcome measures compared to usual medical care, and to examine whether diabetes remission can be achieved. Tackling obesity and diabetes at the earliest stage (younger patients with short diabetes duration) is critical to reducing disease burden with the potential important benefit of reversing diabetes, and preventing its long-term sequelae. The DIADEM-I study aims to implement an ILI incorporating an LED approach in younger T2DM patients with early diabetes.

### Hypothesis

The key hypotheses of DIADEM-I are that an ILI combining an individualised LED approach with physical activity in subjects with early T2DM, compared to the usual medical care (UMC) group, will result in:Greater weight lossImprovement in glycaemic controlPotential remission of diabetesImproved quality of life

### Primary objective

The primary objective of DIADEM-I is to examine the effectiveness of an individualised ILI combining an LED approach and gradual introduction of food with physical activity in younger subjects with early T2DM. The overall aim is to test an intervention that will be successful in weight loss and potential diabetes remission. Remission of diabetes will be defined as:HbA1c outside the diabetes range (< 6.5%)No pharmacologic therapy for diabetes

The ILI will be compared to UMC. The study will examine the primary outcome of weight loss.

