### Study design

DIADEM-I is an open-label, pragmatic, parallel-group RCT, employing the following interventions (Fig. 2):Intensive Lifestyle Intervention (ILI) combining a low-energy diet (LED) approach with physical activity. Behavioural support for the lifestyle intervention will also be providedUsual medical care (UMC) aiming at diabetes education and support, and medical management of glycaemia, hypertension, and dyslipidaemia. This will be based on current clinical practice aiming to reduce diabetes symptoms and complications, and general recommendations on diet and physical activity.

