### Description of Intensive Lifestyle Intervention (ILI)

The primary objective is for subjects to achieve a significant reduction in body weight at 12 weeks and continue progress at 1 year following a diet and physical activity ILI, and maintain this during the follow-up period. Diabetes remission will be assessed throughout the study.

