#### Medications

It is aimed that diabetes medications will be discontinued with the adoption of LED. The process and rate of reduction of any medication will be judged clinically and will depend on symptoms, glycaemic control at baseline, and the subject’s motivation to adopt the LED. Blood pressure medications will be discontinued based on clinical assessments. For the UMC group, any medication intensification will aim to choose diabetes medications that either promote weight loss or are weight neutral.

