#### Schedule of visits (ILI)

Table 3 shows the schedule of intervention visits for the ILI group.

**Table 3 Tab3:** Study phases and visit schedules for the intensive lifestyle intervention

Phase	Timeline	Individual Visit Schedule
1. Low Energy Diet + Physical Activity	Weeks 1–12	Visit every 2 weeks Dietitian (30 min/visit) Exercise trainer (30 min/visit)
		Physician review at baseline and on completion of Phase 1
2. Partial Low Energy Diet + Physical Activity	Weeks 13–24	Visit every 2 weeks Dietitian (30 min/visit) Exercise trainer (30 min/visit)
		Physician review on completion of Phase 2
3. Lifestyle change	Weeks 25–48	Visit every 4 weeks Dietitian (30 min/visit) Exercise trainer (30 min/visit)
		Physician review at 3-month and on completion of Phase 3
4. Follow-up	Weeks 49–96	3 monthly visits for follow-up Dietitian (30 min/visit) Exercise trainer (30 min/visit)
		Physician review at 3-month intervals and completion of Phase 4
5. Post Study	Minimum 2 years post-study	Review by weight management service Collection of data via electronic medical records

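### Remission is defined without a minimum time off diabetes drugs, so subjects who stop late can count as in remission on an HbA1c still lowered by the drug

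*Protocol article*

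**What the plan says.** The Primary objective section gives remission two list items, run together in the extracted text: "HbA1c outside the diabetes range (< 6.5%)No pharmacologic therapy for diabetes". Both describe the subject at the time of assessment. Neither there nor elsewhere does the article ask for a period off drug, a minimum duration of the state, or a repeat HbA1c.

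Three other places bear on how the definition works:

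- **Timing of assessment** (Description of Intensive Lifestyle Intervention): "Diabetes remission will be assessed throughout the study".
- **Drug withdrawal** (Medications): "It is aimed that diabetes medications will be discontinued with the adoption of LED", followed by "The process and rate of reduction of any medication will be judged clinically". For usual care, the same section speaks only of how drugs are chosen when treatment is stepped up: "For the UMC group, any medication intensification will aim to choose diabetes medications that either promote weight loss or are weight neutral".
- **Blinding** (Study design): "DIADEM-I is an open-label, pragmatic, parallel-group RCT".

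Remission is not the primary outcome, which is weight loss at 12 months. It is named among the key outcomes in the Abstract, appears in the Hypothesis section, and is part of the overall aim under Primary objective.

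**The concern.** HbA1c responds to a change in treatment with a delay. A subject may be off drugs on the assessment day while the measured HbA1c still reflects weeks on the drug. The definition counts that subject as in remission, even if the value would settle at 6.5% or above once the drug effect has gone.

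The plan leaves room for this. Stopping with the LED is an aim, the pace is individual, and no date is tied to the HbA1c sample. Because remission is assessed throughout, early assessments count as well as the one at 12 months.

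At stake is the remission comparison. Planned withdrawal is described only in connection with the LED, and those who decide when the last drug stops know the allocation. Misclassification by this route would therefore tend to raise the remission count in the lifestyle arm more than in usual care.

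**Working it through.** The article states no remission rate or carry-over figure, so there is none to reproduce. The check has a textual part and an illustration.

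**Text.** Every section that mentions remission, HbA1c or diabetes medication was read for a drug-free interval. None gives one or refers to another document for one. Primary objective presents the two conditions as the definition.

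**Inputs for the illustration**

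- Drug effect D = 0.5 percentage points. Sample size calculations calls a change of this size comparable to that of most diabetes medications.
- Remission threshold 6.5% (Primary objective).
- How fast HbA1c loses a drug effect: *assumed*, because the article is silent. Model A treats HbA1c as a uniform average of the last 12 weeks. Model B lets the effect decay exponentially with a half-time h of 3 to 5 weeks.
- Settled off-drug HbA1c S: *assumed*, held constant after stopping.

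**Drug effect left w weeks after stopping**

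Model A: D × (12 − w)/12. Model B: D × 0.5^(w/h).

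| Weeks since stop | Model A | Model B, h = 3 to 5 |
|---|---|---|
| 0 | 0.50 | 0.50 |
| 2 | 0.42 | 0.31 to 0.38 |
| 4 | 0.33 | 0.20 to 0.29 |
| 8 | 0.17 | 0.08 to 0.16 |
| 12 | 0 | 0.03 to 0.09 |
| 24 | 0 | 0.00 to 0.02 |

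**One subject, S = 6.8% (6.3% on drug), Model A.** Reading = 6.3 × (12 − w)/12 + 6.8 × w/12.

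- w = 0: 6.30%
- w = 2: 6.38%
- w = 4: 6.47%
- The reading reaches 6.5% when 0.5 × (12 − w)/12 = 0.3, so 12 − w = 7.2 and w = 4.8 weeks.

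**Time to reach 6.5% for other settled values**

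Model A: 12 × [1 − (S − 6.5)/0.5]. Model B: h × log2[0.5/(S − 6.5)].

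| S | Model A | Model B, h = 3 to 5 |
|---|---|---|
| 6.6% | 9.6 weeks | 7.0 to 11.6 weeks |
| 6.8% | 4.8 weeks | 2.2 to 3.7 weeks |
| 6.9% | 2.4 weeks | 1.0 to 1.6 weeks |

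**Who can be misclassified.** The largest carry-over is 0.5, on the day of stopping. A subject with S of 7.0% or more then reads at least 6.5% and does not qualify. A subject with S below 6.5% qualifies correctly. The band at risk is 6.5% to just under 7.0%.

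**What cannot be computed.** The number of false remissions depends on how many subjects stop within weeks of an assessment and how many of those have settled values in this band. The article gives neither.

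**The case against.** The strongest reply is that the plan already limits the problem. Diabetes drugs are meant to stop when the LED is adopted. A subject who does so carries over nothing at 12 weeks under Model A and 0.03 to 0.09 points under Model B, and nothing measurable at 12 months. This stands. It confines the problem to late stoppers and slow taperers, and to assessments close to the stop.

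A reader might infer from Table 3 that drugs are stopped at the end-of-phase physician reviews, on the day outcomes are measured. The article does not support that. Table 3 also lists a review at baseline, when the LED begins. For the later stage it gives "Physician review at 3-month and on completion of Phase 3", without saying that drugs are stopped there. The assessment schedule is in Figure 2, which is not shown.

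A reader might also infer a one-sided bias. That is not established. The same lag works against the lifestyle arm while glycaemia is falling on the LED, because HbA1c still includes earlier, higher values and can miss subjects already below the threshold.

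Finally, the article condenses a fuller protocol, which might set an interval. That is possible, but the article presents a complete definition and points to no further condition. The concern is with the rule as stated, not with detail left out.

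**Conclusion.** The point holds in limited form. As written, the definition counts as remission a subject whose HbA1c is below 6.5% only because a recently stopped drug is still acting on it. With the article's 0.5-point effect, that can last about 5 weeks for a settled value of 6.8% under a uniform 12-week window, 2.2 to 3.7 weeks under the decay model, and longer nearer the threshold. Settled values outside 6.5% to just under 7.0% are not at risk from a drug effect of that size.

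These figures describe assumed subjects under assumed HbA1c kinetics. They do not give the bias in either arm's remission percentage, which is unknown. It would be wrong to conclude that the 12-month remission result is materially inflated. What the text supports is a likely direction: misclassification from drug carry-over would tend to favour the lifestyle arm, because planned withdrawal is described only with the LED and the trial is open-label. The primary outcome, its analysis and the sample size are unaffected. The change should be made because remission is a key outcome and the correction is small.

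**What to change.** Amend the outcome definition, for counting purposes only: remission is HbA1c < 6.5% with no diabetes drug taken since the previous 3-monthly assessment (about 3 months) before the qualifying sample. Apply it identically in both arms. Report the present point-in-time definition as a sensitivity count, so that readers can see how many remissions depend on the interval.

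Three months fits the illustration: after 12 weeks the remaining effect is 0 under Model A and 0.03 to 0.09 points under Model B. It also fits the 12-week length of Phases 1 and 2 and the 3-monthly usual-care attendance.

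The costs are modest. The reported remission percentage may be somewhat lower, and a subject who tapers during Phase 1 cannot qualify at its end. Start and stop dates of diabetes drugs must be captured on the case report form or taken from the electronic record. The article describes both sources but does not say that these dates are recorded, so this needs to be made sure of. No treatment decision changes.
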